### Intervention and control groups

Pregnant women will be randomly assigned into one of four groups. The control group will receive only routine care (newborn eye care, vitamin K_1_, immunizations, weighing, and examinations) after birth, whereas the intervention group will receive EENC including delayed cord clamping, immediate and sustained SSC, initiating exclusive breastfeeding, and routine care. The flow chart of EENC for cesarean section is showed in Fig. 2. Delayed cord clamping is defined as cutting umbilical cord until cord pulsations have ceased (approximately 1–3 min after birth) [18]. Immediate and sustained SSC is regarded as placing of the naked baby prone on the mother’s bare chest immediately after birth without separation [10]. Pairs of mothers and newborns in the intervention group 1, intervention group 2, and intervention group 3 will perform SSC for 30 min, 60 min, and 90 min, respectively.

**Fig. 2 Fig2:**
[figure not shown]
Flow chart of early essential newborn care for cesarean section

### Study outcomes

#### Primary outcomes

The primary outcome is exclusive breastfeeding rates at hospital discharge. Exclusive breastfeeding is defined as feeding only breastmilk with no other food or fluids except medications since birth [4]. Postnatal women will be asked the breastfeeding status of their baby (exclusively breastfeeding [fed only breast milk with the exception of water], main breastfeeding [fed breast milk and water], mixed feeding [fed breast milk, formula milk and water]) since the birth of their baby through the time of the interview at discharge. Another primary outcome is early initiation of breastfeeding defined as the completion of the first breastfeed by a newborn within an hour after birth [19].

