**Methods:**

This is a multi-centered, randomized controlled trial conducted in 4 tertiary hospitals in China. A total of 720 eligible women who will receive cesarean section are being randomized into four groups: control group (*n*=180), intervention group 1 (skin-to-skin contact for 30 min, *n*=180), intervention group 2 (skin-to-skin contact for 60 min, *n*=180), and intervention group 3 (skin-to-skin contact for 90 min, *n*=180). The control group will receive routine care, whereas the intervention groups will receive EENC with different duration of skin-to-skin contact. Demographic characteristics, clinical information, and breastfeeding outcomes will be collected. The primary outcome is rates of exclusive breastfeeding and early initiation of breastfeeding, and the secondary outcomes include maternal and neonatal morbidity and admissions.

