### Sample size calculation

We calculated the sample size based on the rate of early initiation of breastfeeding, which is one of the primary outcomes in this study. According to our pilot investigation and previous literature [4, 20], the rate of early initiation of breastfeeding is 40% in the control group (receiving routine care), and the rates in the intervention group 1 (receiving EENC with SSC for 30 min), intervention group 2 (receiving EENC with SSC for 60 min), and intervention group 3 (receiving EENC with SSC for 90 min) are supposed to be 60%, 70%, and 80%, respectively. Accounting for multiple comparisons (SSC for 30 min vs. routine care, SSC for 60 min vs. routine care, SSC for 90 min vs. routine care, SSC for 30 min vs. SSC for 60 min, SSC for 30 min vs. SSC for 90 min, SSC for 60 min vs. SSC for 90 min), a level of significance is set to be 0.008 (0.05/6) by using Bonferroni adjustments. For 80% power, the sample size required for each of the control group and the intervention group 1 is 152 participants; the sample size required for each of the control group and the intervention group 2 is 64 participants; the sample size required for each of the control group and the intervention group 3 is 34 participants. The largest sample size group (*n*=152) is selected as the number of recruitment in each group. Considering 15% of loss to follow-up, the number of participants in each group is finally set to be 180 and adds up to a total of 720 participants. One hundred eighty participants will need to be recruited in each of four hospitals, which means that each of the hospital will recruit 45 participants in the control group, intervention group 1, intervention group 2, and intervention group 3, respectively. The sample size calculation was performed using PASS 2011 software (NCSS, Kaysville, UT, USA).

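### Early initiation is scored at 60 minutes, so it cannot measure what skin-to-skin contact in minutes 60 to 90 adds; the assumed 70% vs 80% and the 60 vs 90 min comparison have no basis in contact time

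*Protocol article*

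**What the plan says.** **Outcome.** The Primary outcomes section names exclusive breastfeeding at discharge and then early initiation: "Another primary outcome is early initiation of breastfeeding defined as the completion of the first breastfeed by a newborn within an hour after birth".

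**Exposure.** Under Intervention and control groups, immediate and sustained SSC means "placing of the naked baby prone on the mother’s bare chest immediately after birth without separation", and the three intervention groups "will perform SSC for 30 min, 60 min, and 90 min, respectively". The abstract gives duration as the difference between these groups: "the intervention groups will receive EENC with different duration of skin-to-skin contact".

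**Planning.** The Sample size calculation is built on early initiation. It states that "the rate of early initiation of breastfeeding is 40% in the control group" and that the rates with 30, 60 and 90 min of SSC "are supposed to be 60%, 70%, and 80%, respectively". It lists all six pairwise comparisons, 60 vs 90 min included, and sets the significance level at 0.008 (0.05/6).

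**Purpose.** The abstract and the Discussion both promise a recommendation on the optimal duration of SSC. The Background sets the question up as the WHO's one hour against a dose-response through 90 min seen in a cross-sectional observational study.

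**The concern.** An exposure that happens after an outcome is settled cannot influence it. Early initiation is settled at minute 60, and the assigned care of the 60- and 90-min arms first diverges at that minute. If contact starts a little late, the divergence falls after the window has closed. The plan therefore gives a 10-point effect to contact that comes too late to act on this outcome.

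The duration recommendation is at stake. Whether contact beyond the recommended hour helps is the question raised in the Background, and early initiation is one of two primary outcomes expected to answer it. A null 60 vs 90 result on this outcome is what the timing predicts even if longer contact is beneficial, yet it could be reported as evidence that 60 min is enough. A positive result could not be credited to the additional 30 minutes.

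**Working it through.** **1. Assigned contact inside the outcome window.** The window is 0 to 60 min and contact starts at birth, so contact inside the window is min(assigned duration, 60).

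| Arm | Assigned SSC | SSC within 0–60 min | Planned rate |
|---|---|---|---|
| Control | none | 0 | 40% |
| Group 1 | 30 min | 30 min | 60% |
| Group 2 | 60 min | 60 min | 70% |
| Group 3 | 90 min | 60 min | 80% |

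Groups 2 and 3 have the same entry in the third column and different entries in the fourth.

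**2. Reproducing the plan's sample sizes.** Inputs from the Sample size calculation are the rates above, level 0.008 and 80% power; the two-sided test is from the Analysis plan. With the pooled-variance normal approximation and p̄ the mean of the two rates,

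n per arm = [z(0.996)·√(2p̄(1−p̄)) + z(0.80)·√(p1(1−p1) + p2(1−p2))]² / (p1 − p2)², where z(0.996) = 2.652 and z(0.80) = 0.842.

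- 40% vs 60%: (2.652×0.7071 + 0.842×0.6928)² / 0.04 = 151.1, so 152 (stated 152).
- 40% vs 70%: (2.652×0.7036 + 0.842×0.6708)² / 0.09 = 65.6, so 66 (stated 64).
- 40% vs 80%: (2.652×0.6928 + 0.842×0.6325)² / 0.16 = 35.1, so 36 (stated 34).

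The binding figure is exact and the other two are within 2. Allowing for loss, 152 / 0.85 = 178.8, so 179, which the plan sets at 180; 4 × 180 = 720.

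**3. The 60 vs 90 min comparison.**

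- At the plan's own 70% vs 80%, the same formula gives (2.652×0.6124 + 0.842×0.6083)² / 0.01 = 456.2, so 457 per arm. Power at 0.008 is about 26% with 152 per arm and 32% with 180.
- If the two true rates are equal, as the timing implies when allocation has no other effect, the rejection probability is the test level, 0.008. No sample size changes that.

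**4. Effect on the planned numbers.** With a common 70% for groups 2 and 3, control vs 90 min becomes 40% vs 70% and needs about 66 per arm, not the stated 34. The largest requirement is still 152 (control vs 30 min), so 180 per arm and 720 in total stand.

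**5. Optional pooling of groups 2 and 3 against 30 min.** The 30-min rate is 60%, with 152 per arm (304 when pooled) and level 0.008. The common rate is an assumption, so a range is shown.

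| Common rate, groups 2 and 3 | Power, one arm vs 30 min | Power, pooled vs 30 min |
|---|---|---|
| 70% | 20% | 31% |
| 75% | 56% | 73% |
| 80% | 88% | 97% |

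**The case against.** - **The sample size does not depend on the faulty assumption.** This stands. A reader might infer that 720 is wrong or that the trial is undersized for its main question. The documents do not support that: the 80% rate produces only a non-binding requirement. EENC against routine care is unaffected, and an uninformative contrast in a Bonferroni family makes the correction stricter, not looser.
- **Assignment could still make the arms differ.** This also stands. A reader might infer that groups 2 and 3 receive identical care to minute 60 and must show identical rates. Only the assigned contact is shown to be identical. The trial is open-label and analysed by intention to treat. Pairs told 90 min who stop early may still reach 60, while pairs told 60 who stop early do not, and staff may wind down sooner in the 60-min arm. These would be effects of assignment or adherence, not of contact in minutes 60 to 90.
- **Another primary outcome covers duration.** Correct: exclusive breastfeeding at discharge can still separate the two arms. The design can address the contrast, but not through early initiation.
- **Some supporting material is not visible.** The EENC flow chart is not shown, and the planning rates cite a pilot and literature. Nothing in the text gives the two arms different care before minute 60. An observational dose-response through 90 min cannot make later contact the cause of an earlier feed.

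**Conclusion.** The point holds on the protocol's own definitions. On early initiation within an hour, 60 vs 90 min does not test the extra 30 minutes of contact. The 70% vs 80% planning rates cannot reflect that contact, and a null result is not evidence of no benefit beyond 60 min. If the true rates are equal, the chance of a significant finding is 0.8%; the 26% to 32% power at the plan's own rates belongs to a difference that duration cannot produce.

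The damage is confined to this contrast, to the planning figure for control vs 90 min, and to any duration conclusion drawn from this outcome. The comparisons with control remain valid. 60 vs control and 90 vs control share the assigned exposure within the window but use different randomised participants, so they are not duplicates.

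The conclusion assumes that contact starts at the same time after birth in both arms, and that care before minute 60 does not otherwise differ by protocol. The 0.8% further assumes no effect of open-label behaviour or adherence. The 66 per arm assumes a common rate of 70%.

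**What to change.** For early initiation:

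1. Replace 70% and 80% with one common planning rate for groups 2 and 3, and restate the control vs 90 min requirement (about 66 per arm at 70%).
2. Remove 60 vs 90 min from this outcome's comparison family.
3. State that this outcome does not inform 60 vs 90 min, and that neither a null nor a positive result on it will be read as evidence about contact after the first hour.
4. Take the 60 vs 90 min contrast from exclusive breastfeeding at discharge.

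Two additions are optional. Groups 2 and 3 may be pooled against 30 min for this outcome; the gain depends on the unknown common rate, so it should not be quoted as a single figure. Time to first completed breastfeed, over a window longer than 90 min, would let the later contact act on the outcome. It is possible only if clock times were recorded. The protocol does not say that they are, a yes/no field would be enough to score the outcome, and recruitment was expected to end in December 2021.

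The four main changes are wording in the protocol and analysis plan. They need no extra participants and leave assigned care as it is. The cost is an open statement that one of the two primary outcomes says nothing about contact beyond 60 min.

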### Analysis plan

Baseline characteristics of participants will be presented as mean (standard deviation) for continuous variables and number (percentage) for categorical variables. Data will be analyzed on an intention-to-treat basis to compare primary and secondary outcomes in four groups. The chi-square test or one-way analysis of variance will be used to compare the characteristics and rates of exclusive breastfeeding and early initiation of breastfeeding, and maternal and neonatal outcomes among the 4 groups (control group, intervention group 1, intervention group 2, and intervention group 3). For missing data, we will use multiple imputation to obtain complete datasets. All the statistical analyses will be conducted using SPSS 20.0 statistical software (SPSS Inc., Chicago, Illinois). A two-sided *P* value <0.05 indicated significance.

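### Two primary outcomes have no rule linking them, and the Bonferroni divisor and the 80% power cover only one, so an either-outcome claim can carry a false-positive risk of up to about 10%

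*Protocol article*

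**What the plan says.** All places are in the protocol article.

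- **Primary outcomes.** The section opens with "The primary outcome is exclusive breastfeeding rates at hospital discharge" and later adds "Another primary outcome is early initiation of breastfeeding", counted within an hour of birth. It gives no order, no split of alpha and no rule on whether one or both must succeed.
- **Sample size calculation.** Only the second-named outcome is used here: "We calculated the sample size based on the rate of early initiation of breastfeeding, which is one of the primary outcomes in this study". The planning rates are all for that outcome: "the rate of early initiation of breastfeeding is 40% in the control group", and the three intervention rates "are supposed to be 60%, 70%, and 80%, respectively". Six arm pairs are listed, and "a level of significance is set to be 0.008 (0.05/6) by using Bonferroni adjustments". The results are 152, 64 and 34 per group at 80% power; the largest is raised to 180 per group (720 in total) for 15% loss.
- **Analysis plan.** Both primary outcomes are compared among the four groups by chi-square test, and "A two-sided *P* value <0.05 indicated significance".
- **Abstract, Methods.** The two outcomes are joined under a singular primary outcome, which does not say whether both must be significant.

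No expected rate, target difference or power is given for exclusive breastfeeding in this trial.

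**The concern.** The article does not leave multiplicity open. It states a correction and itemises what the correction covers, and the list contains the six arm pairs of one outcome. With two primary outcomes there are twelve pairwise primary tests, or two four-group tests. Half of them lie outside the stated correction, and the significance rule in the Analysis plan makes no allowance for the second outcome. A team that follows the text as written may claim success on whichever outcome is significant, and 5% does not then bound the risk of a false claim.

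The 80% power also describes only the outcome named second. A reader who meets a null result on exclusive breastfeeding could not tell from the plan what difference the trial was able to detect.

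**Working it through.** **Inputs from the article.** Early initiation 40% in control and 60%, 70%, 80% in the intervention groups; planning alpha 0.008 (0.05/6); power 80%; 15% loss; 180 per group; analysis threshold two-sided 0.05.

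**Assumptions, not in the plan.** The correlation between the two outcomes, and a 43% control rate for exclusive breastfeeding. The 43% is the starting value of the vaginal-delivery report cited in the Background.

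**1. Reproduce the plan's figure.** Two-sided comparison of two proportions, pooled variance under the null, no continuity correction, p̄ the mean of the two rates:

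n = [z(1−α/2)·√(2p̄(1−p̄)) + z(0.80)·√(p1(1−p1) + p2(1−p2))]² / (p1−p2)²

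For 40% v 60% at α = 0.008: (2.652 × 0.7071 + 0.8416 × 0.6928)² / 0.04 = 2.4584² / 0.04 = 151.1, so 152. This matches. The other two contrasts give 66 and 36 against the stated 64 and 34, within two participants. Loss: 152/0.85 = 178.8, so 179, set to 180 in the plan; 180 × 0.85 = 153 evaluable.

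**2. Chance of at least one false-positive primary, if either outcome counts.**

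*One four-group test per outcome at 0.05.* Independent outcomes: 1 − 0.95² = 0.0975. Upper bound under any dependence: 0.05 + 0.05 = 0.10. Correlated outcomes come from a normal-approximation simulation (four equal arms, 400,000 runs).

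*Six pairwise tests per outcome at 0.05/6.* Nominal bound: 12 × 0.05/6 = 0.10. The same simulation gives 4.1% for one outcome alone, and for two outcomes the last column below.

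| Assumed correlation | Two four-group tests at 0.05 | Twelve pairwise tests at 0.05/6 |
|---|---|---|
| 0 | 9.8% | 8.2% |
| 0.5 | 9.2% | 7.7% |
| 0.7 | 8.5% | 7.2% |
| 0.9 | 7.2% | 6.0% |

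*If both outcomes had to be significant,* requiring the second would not raise the error rate above that of one outcome.

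**3. Cost of covering all twelve tests.** α = 0.05/12 = 0.00417, z = 2.865. For 40% v 60%: (2.865 × 0.7071 + 0.8416 × 0.6928)² / 0.04 = 2.6091² / 0.04 = 170.2, so 171 per group.

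Power at the planned size = Φ{[0.2·√n − 2.865 × 0.7071] / 0.6928}:
- n = 152: (2.4658 − 2.0260)/0.6928 = 0.635, power 74%
- n = 180: (2.6833 − 2.0260)/0.6928 = 0.949, power 83%

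At 0.05/6 the power with 152 is 81%.

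**4. Exclusive breastfeeding.** Its power cannot be recomputed because no rates are given. From the assumed 43% base, with 152 per group and 80% power, the smallest detectable difference is about 20 points at 0.05/6 and 21 points at 0.05/12. At 0.05/6, power is about 18% for a 10-point and 49% for a 15-point difference. For a rise from 43% to 73%, as in the cited vaginal-delivery report, it exceeds 99%.

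**The case against.** Four things can be said for the plan.

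- **Independence is the unfavourable case.** Both outcomes are breastfeeding measures in the same mother–newborn pairs, so some positive correlation is likely and 9.75% lies close to the ceiling. This stands. A reader might infer that the error rate is simply doubled; the documents support only a figure of up to about 10%, falling to about 7% (four-group tests) or 6% (pairwise tests) at a correlation of 0.9.
- **Both outcomes may be meant to succeed.** There would then be no inflation across outcomes. The wording in the Abstract is compatible with that but does not say it, and neither does any other section.
- **A linking rule is often left to the analysis plan, which is not shown.** This weakens the point but does not remove it. The article itself fixes a divisor, lists its members and states a threshold, and those statements fall short for two primary outcomes.
- **Sizing on one of two primary outcomes is openly disclosed.** True. A reader might infer that exclusive breastfeeding is underpowered. Nothing in the article shows that: the answer runs from about 18% to over 99% according to the assumed effect, and the article gives none for this trial. The gap is that power is not stated.

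Two neighbouring matters are separate and add nothing here. One is that the 0.008 level is not carried into the Analysis plan. The other is that early initiation overlaps with what the intervention package delivers.

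**Conclusion.** The point holds in a bounded form. Two primary outcomes are named, the correction and the power cover early initiation only, and no rule links the two. On an either-outcome reading, the chance of at least one false-positive primary is up to about 10%: 9.75% for two independent four-group tests, about 7 to 9% for correlations of 0.5 to 0.9, and about 6 to 8% for twelve pairwise tests at 0.05/6. These figures rest on that reading, on an assumed correlation and, for the correlated and pairwise cases, on a normal-approximation simulation. The trial's design is not undermined. Its confirmatory claim is not controlled at 5% as written, and the plan should be amended.

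**What to change.** **Preferred.** State that 0.05 is controlled across both primary outcomes, for example by Holm over the twelve pairwise tests. In the Sample size calculation, restate the power for 40% v 60% early initiation as 74% with 152 evaluable per group and 83% with 180. These are Bonferroni figures at 0.05/12 and therefore conservative for Holm.

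**Alternative.** Fix an order of the two outcomes and disclose its power cost. With early initiation first, the planned 80% is kept, and exclusive breastfeeding is confirmatory only where early initiation has succeeded. With exclusive breastfeeding first, confirmatory power for early initiation is capped by the power for exclusive breastfeeding: from the assumed 43% base at 0.05/6, about 18% for a 10-point and 49% for a 15-point difference. If instead both outcomes must be significant, say so.

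**In either case.** Add the detectable difference for exclusive breastfeeding to the Sample size calculation, labelled as an assumption: from a 43% base with 152 per group, about 20 points at 0.05/6 or 21 at 0.05/12.

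**Cost.** Wording only, with no more patients. Under Holm the stated power is slightly lower (74% against 81% at 0.05/6, both at 152). Keeping 80% at 0.05/12 would need 171 evaluable per group, which is 171/0.85 = 202 recruited per group and 808 in total; the fix does not ask for this.

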#### Secondary outcomes

The secondary outcomes include maternal (postpartum hemorrhage, maternal hemoglobin at discharge) and neonatal outcomes (neonatal intensive care unit admission, neonatal ward admission, neonatal weight at discharge [usually 3 days after birth], neonatal transcutaneous bilirubin at discharge).

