### Randomization and blinding

The randomization sequences are generated by the biostatistician using the random number sequence generator function in SAS software version 9.2 (SAS Institute, Cary, NC), with stratification by study sites. Participants will be assigned a randomization code according to their sequential numbers and randomly allocated into one of four groups with a 1:1:1:1 ratio in the operating room. Due to the nature of EENC interventions, blinding of participants, obstetricians, nurses/midwives, and intraoperative research staff is infeasible.

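### Neonatal weight at discharge is planned for a one-way ANOVA that ignores first weight and hospital: a valid test, but probably a much less precise one than the trial's own data would allow

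*Protocol article*

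**What the plan says.** Under Secondary outcomes, the protocol article lists "neonatal weight at discharge [usually 3 days after birth"]. This is an absolute weight, not a change or a percentage loss.

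The Analysis plan section names the tests: "The chi-square test or one-way analysis of variance will be used to compare the characteristics and rates" of the breastfeeding outcomes, and the same sentence extends them to "maternal and neonatal outcomes among the 4 groups". For a continuous outcome that means one-way ANOVA, with arm as the only factor.

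The section on intervention and control groups gives the control arm "routine care (newborn eye care, vitamin K_1_, immunizations, weighing, and examinations"). The EENC arms receive delayed cord clamping and then "immediate and sustained SSC, initiating exclusive breastfeeding, and routine care", so weighing is part of care in every arm.

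Randomization is stratified by study site, and participants are "randomly allocated into one of four groups with a 1:1:1:1 ratio in the operating room".

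**The concern.** One-way ANOVA measures differences between arms against all the variation between babies within an arm. For weight about three days after birth, much of that variation is likely to be birth size, which a first weight would account for. Differences between hospitals go into the same error term, although the randomization is stratified by hospital.

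What is at stake is how much the comparison can tell. Discharge weight is one of the few quantitative neonatal outcomes, and the trial aims to assess neonatal health. If the standard error is large relative to any difference that feeding or skin-to-skin contact could produce, a null result says little, yet could be read as showing no effect or no harm. The primary outcomes and the sample size are not affected.

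**Working it through.** **1. The plan's own figure.** The only sample size in the article is for early initiation of breastfeeding. For 40% vs 60%, two-sided 0.008 and 80% power, the pooled-variance formula for two proportions gives 152 per arm, as stated. Allowing for 15% loss, 152 / 0.85 = 178.8, so 179, against the stated 180. No such figure is given for weight. I use 152 per arm as the number analysed.

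**2. Assumptions.** The documents give no SD for weight, no birth-to-discharge correlation r, and no expected effect. I assume an SD of 400 g and a difference of 50 g, with r from 0.80 to 0.97. I assume no gain from hospital, because nothing in the documents allows one to be calculated.

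**3. Formulas.**
- Unadjusted SE of a difference between two arms = SD × √(2/n) = 400 × √(2/152) = 45.9 g.
- Adjusted SE = unadjusted SE × √(1 − r²).
- Power = Φ(50/SE − 1.96) + Φ(−50/SE − 1.96), two-sided at 0.05 (normal approximation, one pair of arms).
- Difference detectable with 80% power = (1.960 + 0.842) × SE.

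**4. Results.**

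| Analysis | √(1 − r²) | SE (g) | Power for 50 g | Detectable at 80% power (g) |
|---|---|---|---|---|
| Unadjusted | 1 | 45.9 | 19% | 129 |
| r = 0.80 | 0.600 | 27.5 | 44% | 77 |
| r = 0.90 | 0.436 | 20.0 | 71% | 56 |
| r = 0.95 | 0.312 | 14.3 | 94% | 40 |
| r = 0.97 | 0.243 | 11.2 | 99% | 31 |

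**5. When the SE halves.** √(1 − r²) = 0.5 gives r = √0.75 = 0.866. If discharge weight is birth weight plus an independent change, r exceeds 0.866 when the SD of the change is below 0.577 × the birth-weight SD. For a birth-weight SD of 400 g that is about 231 g. Assumed birth-weight SDs of 350 to 450 g with change SDs of 60 to 150 g put r between 0.92 and 0.99.

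**6. Sensitivity of the unadjusted figure.** Power for 50 g is 24% at SD 350 g and 16% at SD 450 g. With all 180 per arm analysed and SD 400 g it is 22%. At the article's Bonferroni level of 0.05/6, with SD 400 g and 152 per arm, it is 6% unadjusted against 45% at r = 0.90 and 97% at r = 0.97.

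**7. What adjustment does to a shift already present in first weight.** The adjusted contrast is the difference in discharge weight minus b times the difference in first weight. With equal SDs, b is about r. If an intervention has already moved first weight and that shift persists to discharge, adjustment removes about a fraction r of it: 80% to 97% over the range above.

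**The case against.** The strongest objection is that first weight is not a true baseline. Allocation is in the operating room, so every weighing follows it. Delayed cord clamping, listed for the EENC arms only, precedes any weighing. Skin-to-skin contact is defined as immediate and without separation. If that is followed literally, first weighing in the EENC arms comes after 30, 60 or 90 minutes, with no such delay in control. Step 7 shows that an adjusted EENC-versus-control contrast could then remove part of a real effect, whereas the unadjusted comparison of randomized arms cannot. This stands and shapes the fix. The 30, 60 and 90 minute arms share the clamping, but their weighing times may still differ.

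Nor does the text shown establish that a timed first weight is a study variable. Weighing is listed as care, and the schedule table and EENC flow chart are not reproduced. It is a reasonable inference, to be confirmed.

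It can also be said that an article leaves covariates to a fuller analysis plan. Here, though, the article names the test for these outcomes, and that test has no covariate. If a fuller plan already specifies adjustment, the article's wording needs only to match it.

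Three stronger readings are tempting but unsupported:

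- **That adjustment is certain to cut the SE by more than half.** This requires r above 0.866, and the documents give no correlation.
- **That chance imbalance in birth weight makes the planned test misleading.** Under the assumptions above, two arms would differ by 50 g or more in birth weight by chance about 28% of the time (2 × [1 − Φ(50/45.9)]). The ANOVA standard error already allows for this, so the type I error rate stays nominal. The loss is of efficiency, not validity.
- **That maternal hemoglobin at discharge should be handled in the same way.** No section mentions a pre-operative value.

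**Conclusion.** The concern holds as a matter of efficiency for one secondary outcome. The planned ANOVA of discharge weight is valid, but it leaves out the stratification factor and a covariate that is very probably available for every newborn. With SD 400 g and 152 per arm, the planned comparison would miss a 50 g difference about four times in five. Adjustment lowers the SE from about 46 g to 28 g at r = 0.80 and to 11 g at r = 0.97. The SD, the correlation and the 50 g are assumptions, but the gain is material even at r = 0.80, where the SE falls by 40%.

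The adjusted EENC-versus-control contrast answers a narrower question than the unadjusted one: the effect on weight change after the first weighing. It should therefore accompany, not replace, a comparison without first weight.

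**What to change.** In the Analysis plan section, replace one-way ANOVA for neonatal weight at discharge with linear regression on arm, hospital and first recorded weight, and report adjusted mean differences with confidence intervals.

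Alongside it:

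- State when first weight is taken relative to skin-to-skin contact in each arm, and confirm that it is recorded as study data.
- For EENC versus control, also report the comparison adjusted for hospital but not for first weight.
- Say that the contrast adjusted for first weight is read as the effect on weight change after the first weighing.

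The cost is a few sentences and one additional model, provided the first weight and its timing are on record. If the time of weighing is not recorded, it would have to be added to data collection or its absence stated as a limitation. No further participants or visits are needed.

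The cost in interpretation is that two estimates are reported for EENC versus control and may differ. If so, the reader needs to know that part of the difference may already have been present at the first weighing.
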